## **Definitions**

The following definitions will be used during the course of the study.

*Clinical malaria.* The primary definition requires: i) the presence of fever (axillary temperature > 37.5 °C) or a history of fever in the past 24 hours; ii) the absence of any other obvious cause of the fever, sign or symptom; iii) the presence of *Plasmodium*. Asexual parasitaemia detected by blood smear and/or by RDT. A secondary definition of malaria will be i) the presence of any sign or symptoms suggestive of malaria; ii) the absence of any other obvious cause of the sign and symptoms; iii) the presence of *Plasmodium*. asexual parasitaemia by blood smear or by RDT.

*Severe malaria.* Severe malaria will be defined according to the WHO criteria [WHO 2000].

*Anaemia.* Anaemia will be defined as Hb concentration <11 g/dl, moderate anaemia as Hb concentration < 8 g/dL and severe anaemia as Hb concentration < 5 g/dl.

*Molecular markers of resistance to SP and AQ.* The mutations at codons 51, 59, and 108 in the dhfr gene, 437 and 540 in the dhps gene, mutations in codon 76 the *P. falciparum* chloroquine transporter gene (pfcr1), and codon 86 of the *P. falciparum* multidrug resistance gene one (pfmdr1) will be monitored.

## **Laboratory Procedures**

*Detection of malaria.* RDT will be used for the initial diagnosis of malaria and to guide treatment according to the guidelines of the NMCP. Parasite prevalence during cross-sectional surveys will be determined using blood smears. Blood films collected at the same time will be read subsequently by two microscopists. Slides which are judged to be discordant for either positivity or parasite density will be read by a third reader. The final result will be the median of the two or three readings.

*Measurement of haemoglobin concentration.* Haemoglobin concentration will be measured colorimetrically using hemoglobin analyzer (Hemocue AB, Angelholm, Sweden).

*Molecular markers of resistance to SP and AQ:* Filter paper samples from children with a mono-infection of *P. falciparum* on blood smears will be analyzed by nested PCR for mutations at codons 51, 59, and 108 of the dhfr gene, 437 and 540 of the dhps gene, 76 of *P. falciparum* chloroquine transporter gene (pfcr), and 86 of the *P. falciparum* multidrug resistance gene one (pfmdr1), according to published methods [Plowe CV et al 1995, Djimde et al 2001, Dicko et al, 2010]. Cases of mixed infection (wild type and mutant) will be categorized as mutant.

*Immunologic assays* will include humoral antimalarial immune response to blood stage and liver stage antigens, cellular antimalarial immune responses to liver stage antigens, levels of cytokines and other host responses (e.g., erythropoietin) measured in sera/plasma or in immune cells / immune cell subsets. Our primary immune endpoints for this study will be humoral immune responses to the well-characterized pre-erythrocytic antigen CSP, and blood stage antigens MSP1 and AMA1. All three antigens are candidate antigens for malaria vaccines, and the Laboratory for Malaria Immunology and Vaccinology developed a highly standardized assays to support preclinical and clinical development of vaccines based on these antigens. Responses to CSP reflect host exposure to the preerythrocytic parasite stages (ie, sporozoites and intrahepatocytic forms), while responses to AMA1 and MSP1 reflect exposure to the blood stage forms of the parasite.

In general, the immune mechanisms that mediate naturally acquired protection from malaria are not conclusively established. For this reason, we will survey a number of humoral and cellular immune responses as secondary or exploratory aspects of the study. For example, preerythrocytic forms of the parasite, when attenuated, can induce sterile immunity in humans, and available evidence suggests that different cellular and humoral immune responses may contribute to

protection. For secondary immunological endpoints of this study, we will survey humoral and cellular immune responses to CSP and novel preerythrocytic antigens that may have a role in protective immunity. LMIV has identified several *P. falciparum* antigens whose orthologues confer protective preerythrocytic immunity in mouse malaria models, including PFL1995c, LISPI, and SAP1.

For blood stage immunity, it is known that naturally acquired IgG antibodies can clear parasite and resolve symptoms when given as passive therapy, but the targets of these antibodies are unknown. In addition to our primary endpoints of antibody levels against AMA1 and MSP1, we will also measure functional activity of blood stage antibodies as secondary endpoints. These include antibodies that will block parasitized red cells from binding to endothelial and other receptors, which many scientists believe should reduce parasite sequestration and therefore malaria-related disease.

Based on the results of our primary and secondary immunologic studies, and the clinical findings of the trial, we may undertake more exploratory assays. For example, if the laboratory or clinical evidence suggests that SMC modulates protective antimalarial immunity, LMIV has genome based tools, such as transcriptomic or proteomic approaches, to broadly survey host responses (plasma, serum, cellular) that may be involved in malaria infection and disease.

### ***Study discontinuation***

Study may be discontinued [if there is](#):

1. Evidence of high level of resistance of *P. falciparum* to SP and AQ determined as prevalence of dhps 540 mutation > 50% or in vivo resistance of *P. falciparum* resistance to SP+AQ > 10%
2. Drastic reduction of the incidence clinical malaria to less than 0.1 episode per child per year without SMC intervention.

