### **General Description of Study Design and Methods:**

The design is a cluster-randomized trial over three years. The target population is children aged 3-59 months old living in Ouelesseboungou district, Mali. In Year 1, villages in four sub-districts will be randomized into four groups (FPD+DOT; FPD+NDOT; DDD+DOT; DDD+NDOT). The optimal mode of delivery will be selected based on the SMC coverage during the first year,

and will then be implemented in villages of two additional sub-districts. Villages in these two sub-districts will be randomized in two groups. Children in the first group will received three rounds of SMC and those in the second group will receive four rounds of SMC to determine the optimal frequency of SMC based on the incidence rate of clinical malaria as measured by passive surveillance. Children in the four sub-districts selected in Year 1 will continue to receive three rounds of SMC in Year 2 using the optimal mode of delivery. In Year 3, children in the randomly selected sub-districts will received SMC by the optimal delivery system determined in Years 1 -2. Immune responses will be measured and compared between the children receiving SMC to a cohort of children not receiving SMC, to assess the impact of SMC on key antimalarial antibody responses over the three year period using cross-sectional surveys at the beginning and the end of the transmission season. Prevalence of malaria infection, anemia and molecular markers of *P. falciparum* resistance to SP and AQ will be measured during these cross-sectional surveys as secondary endpoints in randomly selected sample of the children.

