Another specific objective of this study is to determine whether SMC will increase the spread of SP and AQ resistant parasites. In our previous study that evaluated the impact of SMC during one season on resistance to SP, there was no difference in the frequency of SP resistance markers between parasites collected in treatment and non-treatment villages. It is unknown if longer implementation of SMC will accelerate the accumulation of resistant parasites, nor the status of development of resistance to AQ. Our recent evaluation of IPTp in Tanzania, an area with widespread resistance to SP, IPTp was associated with increased placental parasite density and inflammation. The current study will allow comparing the frequencies of SP and AQ resistance

markers at the beginning of the study and during each subsequent year. The success of SMC in West Africa is due to limited spread of drug resistant parasites, however, changes in parasite population need to be monitored to ensure the effectiveness of this program.

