***Specific objectives***

1. To determine the optimal mode (fixed-point (FPD) vs door-to-door delivery (DDD); directly observed treatment (DOT) vs. non-DOT (NDOT)) and frequency (3 vs. 4 doses per season) of SMC delivery
2. To compare quantitative measures of immunity in children who do and do not receive SMC.
3. To monitor the impact of SMC on the molecular markers of the resistance of *P. falciparum* to SP and AQ.

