### **B. Planned Interim Analyses (if applicable)**

At the end of the first transmission season, data will be analyzed to determine the optimal mode of delivery by comparing primarily the coverage of SMC and secondarily the incidence rate of the clinical malaria between the four intervention arms. In addition, descriptive analysis of the baseline frequencies of the immunological parameters, and molecular markers of the resistance of *P. falciparum* to SP and AQ, will also be performed at the end of Year 1.

Data collected in Year 2 will be used to determine the optimal frequency of the SMC rounds by comparing primarily the incidence of clinical malaria and secondarily the parasite prevalence at the end of season between the 2 arms. Descriptive analysis of immunological parameters and markers of drug resistance will also be performed.

Details of the statistical methods are provided below in the final analysis plan.

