### **B. Human Subjects Considerations**

#### **i. Potential Risks**

Risks to participants in the trial are small. The trial will use only licensed and recommended drugs and does not involve any new methods. The risks to the participants are limited to those associated with the use of SP + AQ and blood sampling. Risks occasionally associated with

finger and heel pricks and venipuncture include pain and bruising at the site of the prick, and rarely infection. Use of SP +AQ can be associated with side effects of the drugs including allergy. Subjects with known allergy to the study drugs will be excluded. Over 800,000 courses of SP and AQ have been given for SMC without any report of a drug associated severe adverse event (SAE), including when surveillance is enhanced [Wilson et al 2011, Ndiaye et al submitted]. However, a potential hazard from the intervention is the possible impact of large scale drug administration over two or three years on the drug sensitivity of malaria parasites. The possibility that SMC with SP+AQ might induce resistance to these drugs in *P. falciparum* has been investigated in a number of trials of SMC. Selection of parasites carrying mutations which confer resistance to pyrimethamine or sulphadoxine has been demonstrated in some but not all studies [Wilson et al]. However, because the prevalence of parasitaemia in children who received SMC was substantially less than in the control group, the total number of parasites carrying resistance markers was less in children who had received SMC than in control children. SP has been used extensively in intermittent preventive treatment in pregnant women and has not be associated with an acceleration of resistance to SP in West Africa. Similarly the use of SP in pilot implementation in Mali was not associated with increased frequency of the molecular markers associated with resistance to SP (Dicko et al 2008). Furthermore, the potential risk of SMC with SP +AQ in inducing resistance of malaria parasite was reviewed carefully by the WHO Technical Expert Group and considered to be an acceptable risk in light of the major benefits conveyed by the intervention. Samples collected on filter paper will be tested for markers of the resistance to SP and AQ at baseline and two years after to monitor the impact of the sensitivity of the malaria parasites to the study drugs as per the WHO recommendations.

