Dans notre précédente étude qui a évalué l'impact de la CPS au cours d'une saison sur la résistance à la SP, il n'y avait pas de différence dans la fréquence des marqueurs de résistance de SP entre les parasites recueillis dans les groupes qui ont reçu le traitement et les groupes qui non pas reçu le traitement. On ne sait pas si la mise en œuvre de la CPS à long terme ne va pas accélérer l'accumulation de parasites résistants, ou le développement de la résistance à SP et AQ. L'évaluation du TPI pendant la grossesse en Tanzanie, une zone avec une résistance généralisée à la SP, a montré que le TPI pendant la grossesse était associé à une augmentation de la densité parasitaire placentaire et l'inflammation. L'étude actuelle va permettre la comparaison des fréquences des marqueurs de résistance à SP et à AQ au début de l'étude et à chaque année de suivi. Le succès de la CPS en Afrique de l'Ouest est dû à une propagation limitée de parasites résistants aux médicaments, cependant, les changements dans la population de parasites doivent être surveillés pour s'assurer de l'efficacité de cette stratégie.

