Cependant, un danger potentiel de l'intervention est l'impact possible de l'administration du médicament à grande échelle sur deux ou trois ans sur la sensibilité des parasites aux médicaments antipaludiques. La possibilité que la CPS avec SP + AQ pourrait induire une résistance à ces médicaments chez *P. falciparum* a été étudiée dans un certain nombre d'essais de la CPS. La sélection des parasites portant des mutations qui confèrent une résistance à la pyriméthamine ou la sulfadoxine a été démontrée dans certaines études mais pas dans d'autres [9]. Toutefois, en raison de la prévalence de la parasitémie chez les enfants qui avaient reçu la CPS était sensiblement inférieure à celle du groupe témoin, le nombre total de parasites portant des marqueurs de résistance était inférieure chez les enfants qui avaient reçu la CPS que chez les enfants dans le groupe contrôle. La SP a été largement utilisée dans le traitement préventif intermittent chez la femme enceinte et n'a pas été associée à une accélération de la résistance à la SP en Afrique de l'Ouest. De même, l'utilisation de la SP dans la mise en œuvre pilote au Mali n'a pas été associée à une augmentation de la fréquence des marqueurs moléculaires de la résistance de *P. falciparum* à la SP [13]. En outre, le risque potentiel de la CPS avec SP + AQ dans l'induction de la résistance des parasites du paludisme a été soigneusement examiné par le groupe d'experts techniques de l'OMS et considéré comme un risque acceptable à la lumière des principaux avantages de l'intervention. Les échantillons recueillis sur du papier filtre seront analysés pour les marqueurs de la résistance à la SP et AQ avant et deux ans après pour suivre l'impact de la CPS sur sensibilité des parasites du paludisme aux médicaments de l'étude, conformément aux recommandations de l'OMS.

La conduite de l'essai n'imposera pas de coûts supplémentaires sur les services de santé locaux. Le projet contribuera aux coûts supplémentaires liés à l'étude ainsi que le renforcement du système de santé dans les zones d'étude.

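### The protocol gives conflicting schedules for the SP/AQ resistance markers, and two of them leave no post-SMC dhps 540 reading before Year 2 dosing

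*Protocol*

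**What the plan says.** The Study discontinuation section (Protocol, section 4) says the study may be stopped on evidence of high resistance, "determined as prevalence of dhps 540 mutation > 50% or in vivo resistance of" P. falciparum to SP+AQ above 10%. The third specific objective is "To monitor the impact of SMC on the molecular markers of the resistance of" P. falciparum to the two drugs.

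The timing of the marker measurements is stated in several places:

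- **General Description of Study Design and Methods:** molecular markers of "resistance to SP and AQ will be measured during these cross-sectional surveys as secondary endpoints". These surveys take place at the start and end of the season over three years.
- **Rationale for This Study:** the study compares frequencies of the "markers at the beginning of the study and during each subsequent year". The French Introduction agrees: "au début de l'étude et à chaque année de suivi".
- **Potential Risks (5.B.i):** filter-paper samples "will be tested for markers of the resistance to SP and AQ at baseline and two years after". The French section 6.4 agrees: "marqueurs de la résistance à la SP et AQ avant et deux ans après".
- **Planned Interim Analyses (5.B):** at the end of Year 1 there is a "descriptive analysis of the baseline frequencies of the immunological parameters, and molecular markers of the resistance of" P. falciparum. The next marker analysis uses the Year 2 data. The French section 5.2 says the same.

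No section says which schedule governs, or when the discontinuation criterion is to be read.

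**The concern.** A yearly comparison and a two-point comparison separated by two years cannot both be the plan. The difference bears on conduct, because one of these markers feeds a discontinuation criterion and Potential Risks itself names loss of drug sensitivity as a potential hazard of the intervention.

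In Year 2, SMC is repeated in the four Year 1 sub-districts and extended to two more. If the field and laboratory teams follow the Potential Risks schedule, or the analysts report only what Planned Interim Analyses lists, that step is taken with no post-SMC dhps 540 result available to those who may invoke the criterion.

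**Working it through.** **Timing.** The protocol has no figure to reproduce here, so the check counts SMC rounds given in the Year 1 sub-districts before the first planned post-SMC reading. From Overall design: SMC starts in August 2014, Year 1 has three rounds, the end-of-season survey is in November/December, and the same children get three further rounds in Year 2, from August 2015.

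| Schedule followed | First post-SMC marker reading | Rounds already given | Before Year 2 SMC? |
|---|---|---|---|
| Summary and Rationale | Year 1 end-of-season survey, Nov/Dec 2014 | 3 | Possible |
| Potential Risks | About two years after the 2014 baseline | 3 + 3 = 6 | No |
| Planned Interim Analyses | Analysis of Year 2 data | 3 + 3 = 6 | No |

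The marker survey at the start of Year 2 does not fill the gap. Overall design places it in the two newly added sub-districts before their first SMC, so it is another baseline.

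**Yield of a Year 1 end-of-season reading.** Inputs:
- 1,784 children surveyed (Sample Size).
- SMC reduces infection by about 80% (Background, which says more than 80%).
- 60% coverage (the Sample Size assumption for the non-optimal methods).
- Untreated parasite prevalence of 20% to 50%. This is my assumption; the protocol gives none.

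Expected smear-positive samples = 1,784 × prevalence × [coverage × 0.2 + (1 − coverage)]. Children not covered are assumed to have no protection, and all positives are taken as P. falciparum mono-infections.

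- Full coverage, factor 0.2: 1,784 × 0.20 × 0.2 = 71; 1,784 × 0.50 × 0.2 = 178.
- 60% coverage, factor 0.6 × 0.2 + 0.4 = 0.52: 1,784 × 0.20 × 0.52 = 186; 1,784 × 0.50 × 0.52 = 464.

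The range is about 70 to 460 samples.

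**Precision.** Clusters: four arms × the minimum of 10 = 40. Design effect = 1 + (n/40 − 1) × ICC. The ICC is assumed to be 0.01 to 0.10, because the protocol's 0.01 comes from vaccine coverage. The 95% half-width at a prevalence of 50% is 1.96 × √(0.25 × design effect / n):

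- n = 71: about 12 points.
- n = 178: 7.5 to 8.5 points.
- n = 464: design effect 1.11 to 2.06, so 4.8 to 6.5 points.

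With a Wilson interval on the effective sample size, the upper 95% limit stays below 50% for an observed prevalence up to about 38% (n = 71), 41–42% (n = 178) or 43–45% (n = 464). The reading is imprecise, but it can still show that prevalence is clearly below the limit.

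**The case against.** Several points against the concern stand.

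- Planned Interim Analyses is an analysis timetable, not a sampling schedule. Describing baseline frequencies at the end of Year 1 is compatible with yearly sampling, and its word for baseline could be read as applying only to the immunological parameters, though the natural reading covers the markers too.
- Potential Risks does not say that testing happens only at those two times. It refers to WHO recommendations and could be read as a minimum.
- The Final Analysis Plan still compares markers between groups.
- The background is reassuring: the Rationale reports no marker difference after one SMC season, and Potential Risks reports no increase in SP markers in the Mali pilot.

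Two stronger readings are tempting, and the protocol supports neither.

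- A reader might infer that the criterion promises a post-SMC safety check between Years 1 and 2, which is then lost. Study discontinuation is permissive, names no date or data source, and is not limited to parasites from SMC recipients. Its companion criterion concerns incidence without SMC, so baseline readings can also inform it.
- A reader might infer from the survey descriptions that markers are never collected at the end of the season, since several lists omit them. Those lists are not exhaustive: Follow-up and measurement of outcomes also omits markers at season onset, where Overall design expressly collects them.

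What remains is the direct contradiction between the yearly and two-year schedules, present in both languages, and the absence of any stated post-SMC marker result at the end of Year 1.

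**Conclusion.** The inconsistency is real and should be corrected. Its size is a matter of timing: the first post-SMC reading in the Year 1 sub-districts comes after three rounds on one schedule and after six on the other two. This says nothing about the chance of crossing 50%, because the protocol gives no baseline dhps 540 prevalence. The conclusion rests on taking the Potential Risks schedule at face value and on the natural reading of the end-of-Year-1 analysis. If both are read generously, the yearly plan survives, but the protocol would still need to say so.

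**What to change.** 1. In Potential Risks and French section 6.4, replace the two-year interval with the yearly schedule of the Rationale.
2. In Planned Interim Analyses and French section 5.2, add that dhps 540 prevalence with its 95% CI from the Year 1 end-of-season survey is reported and considered under Study discontinuation before the Year 2 August round, and likewise before Year 3.
3. Use the P. falciparum mono-infections already eligible for genotyping under Laboratory Procedures. The existing 50% limit can stay.

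The cost is wording in two sections and their French counterparts, plus nested PCR on about 70 to 460 Year 1 samples (under the prevalence and coverage assumptions above) from a survey that already takes blood.

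There are two drawbacks. Precision is limited, as shown above. Infections found soon after SMC may also over-represent mutants: Potential Risks notes such selection in some studies, although the total number of resistant parasites was lower in SMC children. The result should therefore be read beside the pre-SMC baseline and treated as a prompt for review, not an automatic stop.

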### ***Subjects withdrawal criteria and handling***

Withdrawal criteria will include:

- Withdrawal of consent, HIV positive subjects under cotrimoxazole,
- Allergy or intolerance of SMC drugs and

- Travel outside the study villages.

For these subjects the administration of SMC drugs will be discontinued, but subjects will continue to receive routine health care services provided through the health centers in the areas.

